# Long-term effects of motherfit group therapy in pre-(MOTHERFIT1) and post-partum women (MOTHERFIT2) with stress urinary incontinence compared to care-as-usual: study protocol of two multi-centred, randomised controlled trials

**DOI:** 10.1186/s13063-019-3331-6

**Published:** 2019-04-25

**Keywords:** Cost-effective, Group therapy, Motherfit, Pelvic-floor-muscle training, Peri-partum, Post-partum, Pregnancy, Pre-partum, Randomised controlled trial, Stress urinary incontinence

## Abstract

**Background:**

Stress urinary incontinence (SUI) is highly prevalent during pregnancy and after delivery. It is often associated with a failing pelvic floor, sphincteric and/or supportive system. Pelvic-floor-muscle training (PFMT) peri-partum has been proven effective for up to 1 year post-partum; however, its long-term effects are unknown. Group PFMT, given by a physiotherapist, has been proven to be as equally effective as individual therapy. Motherfit is a group-PFMT therapy with an emphasis on pelvic floor exercises, adherence and general fitness. Care-as-usual (CAU), if guideline driven, should, as first treatment option, consist of PFMT. Cost-effective strategies are of relevance, given the rise of health care costs. Motherfit group therapy has the potential to be cost-effective in women with urinary incontinence. Therefore, the objectives of the two current studies are: (1) to investigate whether intensive, supervised, pre-partum (MOTHERFIT1) or post-partum (MOTHERFIT2) pelvic-floor-muscle group therapy reduces 18-month post-partum severity of SUI compared to CAU and (2) whether MOTHERFIT1 OR MOTHERFIT 2 is more (cost-)effective compared to CAU.

**Methods:**

Two multi-centred, randomised controlled trials (MOTHERFIT1, *n* = 150, MOTHERFIT2, *n* = 90) will be performed. Participants will be recruited by their midwife or gynaecologist during their routine check. Participants with SUI will receive either motherfit group therapy or CAU. Motherfit group therapy consists of eight group sessions of 60 min each, instructed and supervised by a registered pelvic physiotherapist. Motherfit group therapy includes instructions on pelvic floor anatomy and how to contract, relax and train the pelvic-floor muscles correctly and is combined with general physical exercises. Adherence during and after motherfit will be stimulated by reinforcement techniques and a mobile app. The primary outcome measure is the absence of self-reported SUI based on the severity sum score of the International Consultation on Incontinence Questionnaire Short Form (ICIQ-UI-SF) at 18 months post-partum. Secondary outcomes evaluate quality of life, subjective improvement and health care costs.

**Discussion:**

The motherfit studies are, to our knowledge, the first studies that evaluate both long-term results and health care costs compared to CAU in pregnant and post-partum women with SUI. If motherfit is shown to be (cost-)effective, implementation in peri-partum care should be considered.

**Trial registration:**

Netherlands Trial Register, ID: NL5816. Registered on 18 July 2016.

**Electronic supplementary material:**

The online version of this article (10.1186/s13063-019-3331-6) contains supplementary material, which is available to authorized users.

## Background

Urinary incontinence (UI) affects 13–40% of women during their life [1–4]. Pregnancy and childbirth are the most important provocative factors for UI during lifetime [5].

Stress urinary incontinence (SUI), defined as any involuntary leakage of urine on effort or exertion, or on sneezing or coughing, is the most prevalent type of UI during pregnancy [6]. SUI can be the result of a failing pelvic floor, sphincteric and/or supportive system [7]. The prevalence of SUI rises from approximately 9% in the first trimester of pregnancy to 32% in the second and 38% in the third trimester [8–10]. Eight weeks after delivery the prevalence of SUI is 19%, rising to, respectively, 22% and 26% at 6 and 12 months post-partum [8, 11]. Mørkved et al. [10] even reported a prevalence of 40% at 8 weeks post-partum. Many women believe that their UI will resolve by itself [12]. However, it is known that 75 to 92% of the women with SUI at3 months post-partum, still have UI even after 5 or 12 years [13, 14]. Often, UI reduces quality of life (QoL) because of its negative impact on sexual relationships and daily life activities [15, 16]. Despite this, 75% of women never seek help for UI because they feel embarrassed or feel that losing urine is normal after giving birth [12, 17, 18].

Pelvic-floor-muscle training (PFMT) aims to improve the supportive system and to achieve a timely contraction in case of expected leakage, both with voluntary (the Knack manoeuvre) and involuntary contractions [19]. Positive effects of PFMT peri-partum are proven up to 1 year post-partum [20]. However, it is still unknown whether the long-term effects are lasting as well as whether pre- or post-partum PFMT is more effective in treating SUI compared to care-as-usual (CAU). Currently there are no guidelines on UI peri-partum for midwifes and gynaecologists [21]. Therefore, CAU is known to be applied differently among health care providers and sometimes only includes prescription of incontinence materials [22]. PFMT may be provided individually or in a group. Recently, a meta-analysis on the effects of individual versus group PFMT for women with UI, both provided by a physiotherapist, showed no significant difference in results between the groups [23]. The latter is of particular interest as group therapy is less expensive when compared to individual therapy, and might, therefore, be a cost-effective strategy. It is known that health care costs are rising due to an increasing level of unhealthy lifestyle and number of people with one or more chronic diseases. For that reason, it is of relevance to focus on the evaluation of potentially cost-effective therapies [24, 25].

Given the promising effects of PFMT in the short term and the potential of group therapy being a cost-effective strategy, the Pelvic care Center Maastricht (PcCM), embedded in the Maastricht University Medical Centre (MUMC+), developed motherfit group therapy. Motherfit group therapy includes pelvic-floor-muscle group therapy (PFMGT) combined with general fitness exercises, provided by pelvic physiotherapists (PPTs), to treat peri-partum women with SUI. Moreover, motherfit group therapy has a strong focus on self-management, as it is reported that this will promote adherence and thereby sustain longer-term effects [26].

The primary objective of this study is to investigate whether a structured assessment and treatment programme (motherfit group therapy) of intensive, supervised PFMGT, including a home maintenance programme, reduces 18 months’ post-partum UI severity (frequency, amount and impact) compared to CAU in adult pregnant women (MOTHERFIT1) and post-partum women with SUI (MOTHERFIT2). The secondary objective is to investigate whether motherfit group therapy is cost-effective compared to CAU in pregnant (MOTHERFIT1) and post-partum women with SUI (MOTHERFIT2) 18 months post-partum.

It is hypothesised that intensive, supervised, pre-partum (study 1: MOTHERFIT1) or post-partum (study 2: MOTHERFIT2) PFMGT is more (cost-)effective compared to CAU in adult pregnant (MOTHERFIT1) or post-partum women with SUI (MOTHERFIT2).

## Methods

### Study design

The study consists of two multi-centred, randomised controlled trials (RCTs), namely MOTHERFIT1 and MOTHERFIT2. MOTHERFIT1 focusses on investigating PFMGT pre-partum and MOTHERFIT2 on PFMGT post-partum. Participants will be recruited in the southern part of The Netherlands from the Maastricht University Medical Center (MUMC+), Zuyderland MC (Heerlen/Sittard), Laurentius Hospital (Roermond), Maxima MC (Eindhoven) and surrounding midwifery practices. Except for Maxima MC, all obstetric centres are part of the Obstetric Consortium Limburg, a first-, second- and third-line obstetric midwifery maternity care collaboration. In every region, a registered PPT will provide motherfit group therapy. This protocol has been prepared in accordance with standard protocol items; recommendation for interventional trials (SPIRIT), a completed SPIRIT checklist is included as Additional file 1.

### Participants

Women will be included if they meet all of the following criteria: (1) aged ≥ 18 years, (2) UI (stress or mixed with predominant stress UI factor, according to Haylen et al. [6], (3) a score of > 3 on the International Consultation on Incontinence Modular Questionnaire-Urinary Incontinence-Short Form (ICIQ-UI-SF) questionnaire [27], (4) are motivated for participation in the motherfit programme, (5) are competent to speak and understand the Dutch language and to read and fill in forms independently and (6) have a mobile app (mApp) on a tablet (Apple or Android) available.

Exclusion criteria are: (1) UI prior to first pregnancy, still existing during pregnancy, (2) high-risk pregnancy, resulting in a contra-indication for performing intensive pelvic-floor-muscle (PFM) exercises (e.g. placenta praevia, vaginal blood loss, preterm uterine contractions), (3) suffering from significant exercise limitations or co-morbidities (physical or psychological) that would restrain a woman from participation in motherfit group therapy, (4) a history of chronic neurological disorders or diseases related to UI (e.g. multiple sclerosis, cerebrovascular accident, diabetes mellitus (during ≥ 1 year with glycated hemoglobin (HbA1c) > 10 mmol/l)), (5) urinary tract infection (urine-sediment, urine culture), (6) a history of anti-incontinence or urogynaecological surgery, (7) women who are expected to be lost to follow-up (e.g. because of a planned change of residency), (8) have had recent pelvic physiotherapy (< 6 months) and (9) refusal to use a mApp.

### Detailed study plan

#### Patient recruitment/consent procedure

The obstetrician/gynaecologist or midwife (case manager) at each centre will be responsible for identifying eligible participants. All women will receive written and digital (www.motherfit.net) general information about the motherfit study at:the first visit to the case manager and may be recruited from the second visit at 12 weeks or later until 27 weeks’ gestation (MOTHERFIT1)routine control at 6 weeks post-partum (MOTHERFIT2)

In case a woman is interested to participate, a simple vaginal examination is performed to check the ability to contract the pelvic floor muscles (Figs. 1 and 2). The woman will receive an envelope containing: patient information, two informed consent forms with return envelope and an information booklet on the medical scientific research of the Dutch Government [28]. The case manager fills in the name, telephone number and email address of the woman at a secure site (digital database), which can only be accessed by the researcher. After 1 week, the researcher will contact the woman by telephone and ask whether she has any questions regarding the study after reading the patient information. If the woman is willing to participate, she will be asked to fill in the two informed consent forms and return them to the researcher. The researcher will sign the two informed consent forms and return one to the participant.

**Fig. 1 Fig1:**
[figure not shown]
Schedule of enrolment, allocation, interventions and assessments for MOTHERFIT1

**Fig. 2 Fig2:**
[figure not shown]
Schedule of enrolment, allocation, interventions and assessments for MOTHERFIT2

### Allocation of participants

After signing the informed consent, the participant will receive an email with a link to the electronic baseline questionnaires. Once the questionnaires are completed, block randomisation (block size is 4) will be done by a computer-generated sequence in a 1:1 ratio on the individual patient and location level. Allocation in blocks of 4 is concealed and done using a central computer. Participants are either allocated to the motherfit programme (intervention) or the CAU (control group).

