### Blinding

Due to the nature of the interventions, the participants and PPTs cannot be blinded. During the trial the coordinating researcher is not blinded. However, once the participant has completed the questionnaires, it is not possible to make changes in the data due to locking of the questionnaires. Moreover, before the statistical analyses all participants will be appointed a new study number for which the coordinating researcher is blinded. Therefore, analyses will be done blinded for treatment allocation.

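### A single fixed block size of 4 by location, with allocations known to unblinded trial staff, lets someone who knows the size and all earlier allocations at a location foresee up to a third of assignments

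*Protocol article*

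**What the plan says.** All references are to the protocol article.

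- **Allocation of participants.** After consent and completion of the baseline questionnaires, "block randomisation (block size is 4) will be done by a computer-generated sequence in a 1:1 ratio on the individual patient and location level". The size is then repeated: "Allocation in blocks of 4 is concealed and done using a central computer". No other block size, and no random variation of size, is mentioned.
- **Blinding.** "Due to the nature of the interventions, the participants and PPTs cannot be blinded", and "During the trial the coordinating researcher is not blinded". The safeguards given are that completed questionnaires are locked and that participants are renumbered before analysis.
- **Patient recruitment/consent procedure.** The case manager at each centre identifies eligible women and enters their contact details in a database open only to the researcher. After one week, "the researcher will contact the woman by telephone and ask whether she has any questions regarding the study". That person also receives, signs and returns the consent forms. All of this comes before randomisation.
- **Participants.** Motivation to take part in the programme is an inclusion criterion.
- **Primary outcome measure.** The outcome is a self-reported symptom score.

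**The concern.** Central allocation keeps the list out of sight. When every block has the same known size, though, the end of each block follows from what has already been assigned. Once two women in a block of 4 have gone to one arm, the rest of that block is fixed. The two safeguards under Blinding protect the data and the analysis. They do not affect who is enrolled or when.

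Anyone who can infer the next arm and also speaks to candidates before randomisation has room to encourage one woman a little more, or to time a contact. In this trial, selection of that kind would bear on the result. The women who score the primary outcome know their arm, motivation is an entry criterion, and the Discussion describes adherence as strongly predictive of long-term results. If more motivated women tended to enter one arm, part of the difference at 18 months post-partum would reflect who was enrolled and not what they received.

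**Working it through.** The article gives no predictability figure, so there is none to reproduce.

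**Inputs from the article:** block size 4 and 1:1 ratio, hence 2 + 2 per block; allocation by location (Allocation of participants); 150 women in MOTHERFIT1 and 90 in MOTHERFIT2 (Sample size calculation).

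**Assumptions:** separate sequences for the two trials; four or five locations of equal size. Study design names four hospital organisations and Trial status mentions five regions, but the unit meant by location is not defined.

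**Step 1: complete blocks.** There are 6 equally likely orders of two A and two B. An assignment is certain when one arm's two places are already used. The best guess is the arm that is behind, or a coin toss when the arms are level.

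| Position in block | Probability certain | Probability best guess is right |
|---|---|---|
| 1 | 0 | 1/2 |
| 2 | 0 | 2/3 |
| 3 | 1/3 | 2/3 × 1/2 + 1/3 × 1 = 2/3 |
| 4 | 1 | 1 |
| Sum | 4/3 | 17/6 |
| Divided by 4 | 1/3 = 33.3% | 17/24 = 70.8% |

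Without knowledge of earlier allocations these figures would be 0% and 50%.

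**Step 2: incomplete last blocks.** Each full block contributes 4/3 certain assignments. A last block with one or two women contributes none.

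| Trial | Locations | Women per location | Certain assignments | Share |
|---|---|---|---|---|
| MOTHERFIT1 | 4 | 37 (9 blocks + 1) | 4 × 9 × 4/3 = 48.0 | 48.0/148 = 32.4% |
| MOTHERFIT1 | 5 | 30 (7 blocks + 2) | 5 × 7 × 4/3 = 46.7 | 46.7/150 = 31.1% |
| MOTHERFIT2 | 4 | 22 (5 blocks + 2) | 4 × 5 × 4/3 = 26.7 | 26.7/88 = 30.3% |
| MOTHERFIT2 | 5 | 18 (4 blocks + 2) | 5 × 4 × 4/3 = 26.7 | 26.7/90 = 29.6% |

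Over both trials this is 48.0 + 26.7 = 74.7 with four locations and 46.7 + 26.7 = 73.3 with five, so roughly 75 of 240.

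**Step 3: varying the block size.** This was simulated for 30 women per location (an assumption). The observer sees all earlier allocations at the location and knows which sizes may occur, but not their order.

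| Block sizes | Certain | Best guess right |
|---|---|---|
| 4, fixed | 31.0% | 70.1% |
| 2, 4, 6 | 3.9% | 69.9% |
| 4, 6 | 5.6% | 68.8% |
| 4, 6, 8 | 2.4% | 67.5% |

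Varying the size removes most of the certainty but lowers best-guess accuracy only modestly. With size 2 in the mix, that accuracy hardly moves. A larger fixed size does less about certainty: for complete blocks, 25% of assignments stay certain with size 6 and 20% with size 8.

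**Step 4: how many women a change could reach.** Trial status expects the last follow-up in August 2020. Eighteen months earlier is February 2019 for the last delivery, and six weeks after that is about March or April 2019 for the last MOTHERFIT2 entry. The article is dated 25 April 2019 but says that recruitment is still under way.

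**The case against.** The case on the other side has real force.

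- **Who makes the call.** A reader might infer that the unblinded coordinating researcher makes the recruitment call. The article speaks of the researcher in one section and the coordinating researcher in another and never equates them. The inference is plausible but not stated.
- **The steps before randomisation.** The case manager, not the researcher, identifies candidates, and the call is set at one week. The woman must then return her forms and finish the questionnaires. Her place in the sequence depends on when she finishes and on who else is pending at that location, so the next arm at the time of the call need not be hers. This narrows the opportunity without closing it.
- **What the observer must know.** The one-third figure needs the block size and every earlier allocation at the location. A single midwifery practice may see only part of the sequence, and the training described for case managers and therapists does not mention block size. An unblinded coordinator can have the full picture, however, and the size now stands in a published article.
- **Adjustment.** Analysis of main hypotheses adjusts for the baseline score and considers BMI, parity, age and ability to contract the pelvic floor. Selection on those factors would be partly handled, so it would be too strong to say that nothing can be corrected afterwards. Motivation is not among them.
- **A common design.** Central allocation in permuted blocks within site is usual and is stated here as concealed. That is true, but concealing the list does not prevent inference from known past assignments.

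**Conclusion.** The point holds as an avoidable weakness in the allocation rule. For a person who knows the block size and all earlier allocations at a location, one third of assignments are certain in complete blocks, and about 30–32% (roughly 75 of 240) under the assumed four or five equal locations. That person's best guess is right about 70% of the time. Smaller locations would mean more incomplete blocks and a lower share of certain assignments. The wording "on the individual patient and location level" is loose; if blocks were not kept by location, the same third would apply to someone who sees all allocations.

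Two stronger readings are tempting and not supported. One is that 80 of 240 assignments are predictable to those who recruit. That takes every block as complete and gives recruiters knowledge the article does not attribute to them. The other is that enrolment was in fact steered. The article shows only that it could have been.

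**What to change.** **Women still to be randomised**

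- Let the central system draw block sizes at random within location, avoid size 2 (for example 4, 6 and 8), and do not disclose the sizes to anyone who recruits or in any publication during recruitment. Keep location as the stratum.
- Where existing staff allow, keep anyone who knows earlier allocations out of the recruitment call and the consent step.
- State whether the person who calls candidates is the coordinating researcher, and define the unit meant by location.

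**Women already randomised**, who on the article's own timetable may be most of the sample

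- Report who knew the block size and the earlier allocations during recruitment.
- Rebuild the sequence for each location, classify each woman by the arm that the earlier allocations made more likely (motherfit, CAU or even), and compare baseline characteristics across these classes. A pattern would suggest selection. The absence of one would not exclude selection on unmeasured motivation.

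**Cost.** A change to the randomisation program, a short amendment and one descriptive table. The downside is slightly larger chance imbalance within small locations: an interrupted block of 8 can leave the arms 4 apart, against 2 for a block of 4.

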### Blinding

Due to the nature of the interventions, the participants and PPTs cannot be blinded. During the trial the coordinating researcher is not blinded. However, once the participant has completed the questionnaires, it is not possible to make changes in the data due to locking of the questionnaires. Moreover, before the statistical analyses all participants will be appointed a new study number for which the coordinating researcher is blinded. Therefore, analyses will be done blinded for treatment allocation.

### Protocol training

#### Case managers

Preceding the inclusion period, on-site information, instruction on the standardised assessment and inclusion procedures will be provided to case managers by the researcher for 1 h. Assessment follows the standard procedures of the Dutch Consortium Urogynecology to assess pelvic floor signs and symptoms. Special attention will be paid to the short assessment of a correct contraction of the PFMs by observation and vaginal palpation for closing and lifting of the PFMs [29].

### Pelvic physiotherapists (PPTs)

In The Netherlands, pelvic physiotherapy is a specialisation within the field of physiotherapy and has its own registration in order to guarantee quality [30].

Preceding the inclusion period, information, instruction and training on the standardised assessment and group therapy protocol will be provided to involved PPTs during a 2-h workshop. The PPTs receive a set of laminated A4 papers with a detailed description for each therapy session, containing: topics to discuss, PFM and homework exercises.

### Interventions

#### Care-as-usual

In case participants with SUI are allocated to the CAU group, participating case managers give their normal advice and women make their own choices as to whether they want to participate in any kind of pregnancy-related course, visit to a physician or therapist.

#### Motherfit group therapy

All women allocated to motherfit group therapy, and unaware or unable to contract their PFMs correctly, will be referred to the PPT for individual instruction before joining the motherfit group therapy (Fig. 3). Every participating region has a PPT who provides individual or group therapy. Motherfit consists of eight group therapy sessions of 60 min each, instructed and supervised by a registered PPT. In each group a maximum of four women are allowed to participate. Women of both studies can start when they have been randomised to motherfit group therapy. Therefore, the participant’s group composition may change over time. Motherfit includes instructions on pelvic floor anatomy and how to contract, relax and train the PFMs correctly and is combined with general physical exercises with a strong focus on self-management.

